**<Study design>**

1. 0-1month: Get approval from IRB
2. 2-13 months: patients’ enrollment
3. 14-25 months: follow up with laboratory test
4. 26-36 months: analysis and report

**<Methods>**

- Selecting patients who satisfy inclusion and exclusion criteria
- Randomization (without blinding):
  - Experiment arm: Roux-en-Y gastrojejunostomy
  - Control arm: Gastroduodenostomy
- Laboratory follow up: preoperation, post-operative day#7, #3months, #12 months
- Weight, fasting sugar level, post prandial 2hr sugar level, HbA1c, C-peptide (both of fasting and post prandial 2hr), lipid profile, insulin (both of fasting and post prandial 2hr), glucagon, IGF-1, GLP-1, Neuropeptide Y, Ghrelin, Leptin
- HOMA scale: HI=plasma glucose(mmol.L) x insulin(UI/ml)/22.5
- Comparing the outcomes between Roux-en-Y gastrojejunostomy and Gastroduodenostomy

1. **Variables**

-height, weight

-blood pressure, pulse rate

-duration of DM, duration of DM treatment, drug for DM

-insulin or not and amount

-pathology, postoperative morbidity and mortality

-Weight, fasting sugar level, post prandial 2hr sugar level, HbA1c, C-peptide (both of fasting and post prandial 2hr), lipid profile, insulin (both of fasting and post prandial 2hr), glucagon, IGF-1, GLP-1, Neuropeptide Y, Ghrelin, Leptin

- Laboratory follow up: preoperation, post-operative day#7, #3months, #12 months

-questionaire for quality of life

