**Surgical treatment for patients with gastric cancer and type II DM.**

Gastrectomy for gastric cancer leads weight loss of patient and sometimes the patient experience resolution of co-morbidity such as hypertension and DM. Therefore, modifying gastric cancer surgery with adaption of metabolic surgery could improve DM more efficiently. The main procedure for gastric cancer surgery is that resection of stomach including cancer and lymph node dissection. The extent of gastrectomy is decided not by the presence of DM but by location of tumor and surgeon’s preferences; gastroduodenostomy, gastrojejunostomy with loop type, and Roux-en-Y gastrojejunostomy are the common reconstruction type. The type of reconstruction is known that it is not related to the patients’ prognosis. Recent study reported that subtotal gastrectomy with Roux-en-Y reconstruction for gastric cancer was related improvement of DM; 57% of patients were not required any medication for DM at 1 year after gastrectomy. Thus, this study is going to compare the outcome of DM improvement after subtotal gastrectomy for patients with gastric cancer and DM between Roux-en-Y gastrojejunostomy and gastroduodenostomy.

[figure not shown]

[figure not shown]

(Roux-en-Y gastrojejunostomy) (Gastroduodenostomy)

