# Gastroduodenostomy

Gastroduodenostomy was performed using circular staple and the common channel was repaired by linear stapler after standard gastrectomy with lymphadenectomy.

Until now, no randomized controlled trial has been conducted for comparing the efficacy of DM improvement according to reconstruction type for gastric cancer surgery.

1. **Purpose**
2. Comparing the effect of improvement of hyperglycemia according to reconstruction type (Roux-en-Y gastrojejunostomy vs. gastroduodenostomy) in patients with gastric cancer and DM
3. Evaluating the mechanism of DM improvement according to reconstruction type.
4. **Place and period of the study**

Place: Severance hospital, Yonsei University College of Medicine

Periods: 2011.05.01~2014.04.30 (36 months)

1. **Selection criteria**

Inclusion criteria

1. Plan to underwent surgery for early gastric cancer, and in treatment for diagnosed DM and/or newly diagnosed DM in pre-operative check up
2. Location of tumor is lower part of stomach (possible cases of distal gastrectomy)
3. Age between 20-80
4. Understand the study and informed consent patients

Exclusion criteria

1. Patients who were treated by systemic inflammatory disease or with other malignancy
2. Uncontrolled co-morbidity
3. Vulnerable subjects (minor, pregnant women, lack of ability of recognition)
4. Severe complication after gastrectomy
5. **Sample size**

Retrospective study from our institution showed that proportion of patients who experience complete remission of DM, which was defined as no more necessity drug to control DM, was around 15% after gastroduodenostomy. It was reported that around 57% of patients who underwent Roux-en-Y gastrojejunostomy for gastric cancer with DM experienced remission of DM. Thus sample size for each group will be 18 for 0.05 of alpha and 0.20 of beta, and estimating 10% of drop-out rate, total 40 patients will be required.

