**Evaluation**

-Improvement of laboratory data about DM after surgery

-Decreasing of drug to control DM or remission of DM

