**Statistical analysis**

- t-test, Chi-square test, Log-rank test, ANOVA test or Kruskal-wallis test

- HbA1c, C-peptide, lipid profile, Insulin, glucagon, IGF-1, GLP-1, Neuropeptide Y, Ghrelin, Leptin, HOMA scale: as an longitudinal data, comparing them by repeated measurement analysis of variance (RMANOVA) for comparing between Roux-en-Y gastrojejunostomy and Gastroduodenostomy

-two side p-value of less than 0.05 will be considered as statistical significance

1. Criteria for evaluation of safety, including side effects, evaluation methods and reporting methods

There are no changes in the existing surgical methods and data collection process, so there is no plan to report any postoperative complications or side effects.

1. Interim analysis

There is no planed interim analysis in this study.

1. Monitoring for data, process, and safety of this study

Investigator will do regular check.

1. Time table for the study

|  | **추진일정 (월)** | | | | | |
| --- | --- | --- | --- | --- | --- | --- |
|  | **0-1** | **2-13** | | **14-25** | **26-30** | **31-36** |
| **IRB Approval** |  |  | |  |  |  |
| **Patients’ enrollment** |  |  |  |  |  |  |
| **Data collection** |  |  |  |  |  |  |
| **Patients’ follow up** |  |  |  |  |  |  |
| **Analysis** |  |  |  |  |  |  |
| **Report** |  |  |  |  |  |  |

1. References

1) Joshua PT, David EC Cummings Hormonal and Metabolic Mechanisms of Diabetes Remission after Gastrointestinal Surgery. Endocrinology 2009 150:2518-2525

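### No visit is named for judging improvement or remission, although the 57% planning rate is a 1-year rate, and the between-arm RMANOVA of HbA1c takes in day 7

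*Protocol*

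**What the plan says.** - **Schedule.** Protocol, Methods: "Laboratory follow up: preoperation, post-operative day#7, #3months, #12 months". The line appears again under Variables. One panel hangs on it, with HbA1c and 2-hour post-prandial glucose among the markers, and no marker is exempted at any visit.
- **Laboratory analysis.** Protocol, Statistical analysis: HbA1c and the other markers are treated "as an longitudinal data, comparing them by repeated measurement analysis of variance (RMANOVA"), between the two reconstructions. No visit is named as decisive, and the model term to be tested is not given.
- **Other tests.** The same section lists "t-test, Chi-square test, Log-rank test, ANOVA test or Kruskal-wallis test" without attaching any of them to an endpoint.
- **Criteria.** Protocol, Evaluation: "Improvement of laboratory data about DM after surgery" and "Decreasing of drug to control DM or remission of DM". Neither has a time point.
- **Remission.** Protocol, Sample size: "complete remission of DM, which was defined as no more necessity drug to control DM", with no visit and no minimum duration.
- **Origin of the planning rate.** Protocol, background on gastric cancer with type II DM: "57% of patients were not required any medication for DM at 1 year after gastrectomy". The Sample size section reuses the 57% without the year and gives no time point for the 15% control rate.

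**The concern.** The question is whether reconstruction type improves diabetes. The trial is sized on a rate observed at 1 year, but that year is not carried into the outcome. With 40 patients, open allocation and three post-operative visits, the visit that decides the result could be chosen after the data are seen.

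The analysis that is fixed, RMANOVA of HbA1c over the scheduled visits, brings in a value that can say little about the operation. HbA1c averages glycaemia over weeks to months (general knowledge of the marker, not a statement in the protocol), so one week after surgery it is still mostly a pre-operative measurement in both arms. If the arms are compared on their average over visits, that value pulls the contrast towards zero.

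**Working it through.** **1. The plan's own figure.** Inputs from the Sample size section and its power output: 0.57 versus 0.15, 18 per arm, two-sided likelihood ratio test, target alpha 0.05. Exact binomial enumeration gives power 0.8091 and actual alpha 0.0764, both as printed. Dropout: 36/(1 − 0.10) = 40, also as printed. No time point enters this calculation, so the present point does not alter it. The time point matters for what the 0.57 refers to.

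**2. Assumptions for the HbA1c illustration** (none is in the documents): arm difference 0 at day 7 and D at both 3 and 12 months; equal SD at all visits; the same correlation ρ between any two visits, taken as 0.3, 0.6 and 0.8.

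**3. Group effect averaged over the three post-operative visits.**
- Contrast: (0 + D + D)/3 = 2D/3.
- Variance of a patient's three-visit mean, in units of SD²: (1 + 2ρ)/3.
- Signal-to-noise in units of D/SD: r = (2/3)/√[(1 + 2ρ)/3]. For 12 months alone, r = 1.
- Sample-size ratio against 12 months alone: 1/r² = (3/4)(1 + 2ρ).

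| ρ | Variance of mean | r | Ratio |
|---|---|---|---|
| 0.3 | 1.6/3 = 0.533 | 0.913 | 1.20 |
| 0.6 | 2.2/3 = 0.733 | 0.779 | 1.65 |
| 0.8 | 2.6/3 = 0.867 | 0.716 | 1.95 |

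The ratio equals 1 at ρ = 1/6; below that, averaging more visits would outweigh the dilution.

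**4. The same in power.** Choose D to give 80% power at 12 months alone with 18 per arm: D = (1.960 + 0.842) × √(2/18) = 0.934 SD. Power for the averaged contrast is Φ(2.802r − 1.960).
- Three post-operative visits: 72% at ρ = 0.3, 59% at 0.6, 52% at 0.8.
- Pre-operative value also averaged in: contrast 2D/4 = D/2 and r = 0.5/√[(1 + 3ρ)/4], which gives 53%, 39% and 33%.

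**5. If group-by-time is tested instead.** The visits are not averaged, so a zero difference at day 7 does not shrink the contrast; day-7 HbA1c acts much like a second baseline. Such a test can, however, be significant because of any one visit, so by itself it does not establish a difference at 12 months.

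**The case against.** The best defence is that much of this is silence. The quoted line is a laboratory schedule and does not say how day 7 bears on efficacy. The model term and the endpoint of each listed test are matters commonly left to a statistical analysis plan, which is not at hand. Day 7 also has a legitimate use: the second stated purpose is mechanism, and hormones are sampled at the follow-up points. The background further cites improvement after duodenal bypass without notable weight loss, so an early arm difference in glucose or hormones is plausible. All of this stands, and it is why the figures above are confined to HbA1c and to one possible test.

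It does not remove the point. The protocol itself chooses RMANOVA over the scheduled visits for HbA1c, and it states the outcome criteria without the year attached to its planning rate.

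Three stronger readings are tempting but unsupported:
- *Day 7 counts on equal terms with 12 months.* A reader might infer this from an unranked list; the protocol does not say it.
- *Short-lived remissions count as events.* Day 7 is a laboratory visit only. Drug use is listed under Variables with no visit attached, and the log-rank test has no named endpoint. Nor do the documents say that surgery changes drug need transiently.
- *Including day 7 costs about half the patients.* That figure compares with the average of 3 and 12 months: (1/0.80)/(0.444/0.733) = 2.06 at ρ = 0.6. The comparison recommended here is 12 months alone, for which the ratio is 1.65.

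**Conclusion.** The point holds in limited form. The protocol fixes no visit for judging improvement or remission, although its treatment-arm planning rate is a 1-year rate, and its RMANOVA admits day-7 HbA1c to the between-arm comparison. The first part rests on the text alone. The loss from the second is conditional on the group effect being the test, no HbA1c difference at day 7, the full difference by 3 months, and equal variances and correlations. Under those assumptions the sample-size ratio is about 1.65, with a range of 1.20 to 1.95. With a group-by-time test this dilution does not arise. The stated sample size is unaffected. A 12-month comparison is the better choice because it matches the planning rate and the last scheduled visit.

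**What to change.** In Evaluation and Statistical analysis:
- Define the remission outcome as remission at the 12-month visit and compare the arms as proportions. If the log-rank test was meant for remission, replace it with this comparison.
- Make the laboratory efficacy comparison the 12-month difference between arms, adjusted for the pre-operative value, with 3 months supportive.
- Leave day-7 HbA1c out of the efficacy comparison.
- Assign day-7 glucose, insulin and hormones to the mechanism aim only.

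The cost is protocol wording, with no added visit. The drawback is that day-7 data no longer contribute to the efficacy claim.

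### HOMA and measured insulin are compared between arms with no provision for patients who inject insulin, so unequal stopping of injections could pass for a change in insulin resistance

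*Protocol*

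**What the plan says.** - **Who is admitted.** Under Selection criteria, the diabetes requirement is "in treatment for diagnosed DM and/or newly diagnosed DM in pre-operative check up". None of the four exclusions concerns insulin therapy.
- **What is recorded.** The Variables list includes "insulin or not and amount". Insulin and C-peptide are each measured fasting and two hours after a meal, before surgery and at day 7, 3 months and 12 months.
- **The index.** Under Methods: "HOMA scale: HI=plasma glucose(mmol.L) x insulin(UI/ml)/22.5". The formula does not say whether fasting or post-prandial values enter it.
- **The analysis.** Under Statistical analysis, HbA1c, C-peptide, insulin, HOMA and the gut and appetite hormones are treated as longitudinal data, "comparing them by repeated measurement analysis of variance (RMANOVA") between the two reconstructions. No subset and no handling of insulin users is stated.
- **The purpose served.** The second aim is "Evaluating the mechanism of DM improvement according to reconstruction type".
- **Expected drug withdrawal.** Under Sample size, drug-free remission is put at about 15% after gastroduodenostomy, and remission at about 57% after Roux-en-Y. The background describes a 57% result as patients needing no diabetes medication at one year. Reduction of diabetes drugs is itself listed under Evaluation.

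**The concern.** HOMA as defined is proportional to whatever insulin the assay reads. In a patient who injects, that reading can contain the injection as well as the patient's own secretion, so the product no longer measures resistance. Randomisation balances insulin use before surgery on average. It does not balance stopping after surgery, which the trial expects to depend on the arm.

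An arm difference in HOMA could therefore be a by-product of drug withdrawal, which the trial already counts as an outcome, and yet be reported as evidence on mechanism. For measured insulin the problem is one of interpretation: a change cannot be attributed to the patient's own secretion. The eight-hour fast under Evaluation of hormonal change does not settle this, because it says nothing about injected insulin.

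**Working it through.** **The plan's own calculation.** The only design figure is for remission. Exact binomial enumeration of the two-sided likelihood ratio test, with 18 per arm and 57% against 15%, gives power 0.8091 and actual alpha 0.0764, as printed. Allowing for 10% drop-out, 18/0.9 = 20 per arm, 40 in total. This point does not rest on those figures.

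**Inputs from the protocol.** The HOMA formula with divisor 22.5, and the remission rates 0.57 and 0.15.

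**Inputs assumed, because the protocol gives none.**
- Share of insulin users at baseline, f: 0.10 to 0.30.
- Amount that injected insulin adds to the assay reading, X: 5 to 30 microU/mL.
- Glucose, G: 8 mmol/L.
- Own insulin, E: 10 microU/mL.
- G and E are unchanged by surgery or by stopping injections.
- Insulin users stop at the remission rates. These are rates of needing no drug at all among diabetic patients, not rates of stopping insulin among its users.

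**One patient.** While injecting, HOMA = G(E + X)/22.5. After stopping, HOMA = GE/22.5 = 8 × 10/22.5 = 3.56.

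| X | HOMA while injecting | Fall on stopping | Glucose that would cancel the fall, G(E + X)/E |
|---|---|---|---|
| 5 | 5.33 | 33% | 12 mmol/L |
| 10 | 7.11 | 50% | 16 mmol/L |
| 20 | 10.67 | 67% | 24 mmol/L |
| 30 | 14.22 | 75% | 32 mmol/L |

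Resistance is the same before and after in every row.

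**Arm difference in mean HOMA change.** This is f × (0.57 − 0.15) × G × X/22.5 = f × X × 0.42 × 8/22.5 = 0.1493 × f × X.

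| f | X = 5 | X = 10 | X = 20 | X = 30 |
|---|---|---|---|---|
| 0.10 | 0.07 | 0.15 | 0.30 | 0.45 |
| 0.20 | 0.15 | 0.30 | 0.60 | 0.90 |
| 0.30 | 0.22 | 0.45 | 0.90 | 1.34 |

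The baseline mean is 8 × (10 + fX)/22.5. It is 3.73 at the smallest corner and 6.76 at the largest, so the artefact runs from 0.07/3.73 = 2% to 1.34/6.76 = 20% of baseline. It scales directly with the gap in stopping rates and with the fraction of injected insulin that the assay detects: halving either halves every entry, and zero in either gives zero.

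**In patients.** With 20 per arm, f of 0.10 to 0.30 means 2 to 6 users per arm. A gap of 0.42 is then 0.8 to 2.5 patients.

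**The case against.** Several points count against a stronger version, and most of them stand.

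- **Population.** A reader might infer that the protocol orders the analysis in all patients. It does not use those words; it only states no restriction, and an analysis plan that is not shown could add one. What remains is that the protocol itself fixes the index, the variables and the between-arm method, and that this index is unsuitable for patients it admits. That is more than missing detail.
- **Stopping rates.** A reader might take 57% and 15% as the trial's forecast of insulin stopping. They are remission rates. They support an expectation that treatment is withdrawn more often after Roux-en-Y, but not the size of the gap among insulin users.
- **Direction.** A reader might infer that both variables are biased towards the hypothesis. This holds for HOMA only. The background expects GLP-1 to raise insulin secretion, so a spurious fall in measured insulin after Roux-en-Y would work against that part of the hypothesis.
- **Assay and offsets.** No insulin assay is named; the listed kits cover other hormones. Without detection of injected insulin there is no artefact. A rise in glucose or in own secretion after stopping would offset part of the fall.
- **Significance.** No standard deviation for HOMA is given, so nothing shows that such an artefact would produce a small p-value.
- **Existing safeguards.** C-peptide is already measured at each laboratory visit and is already in the repeated-measures list, and several other hormones also serve the mechanism aim. This limits the damage and makes the remedy cheap, but it does not correct the HOMA comparison.

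**Conclusion.** The point holds as a conditional weakness in the mechanism analysis. If insulin users enrol, the assay detects injected insulin, injections are stopped more often after Roux-en-Y, and glucose or own secretion does not rise enough to compensate, HOMA will fall more in that arm with no difference in resistance. Measured insulin will likewise not be interpretable as own secretion.

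The size is unknown. About 0.1 to 1.3 HOMA units is an illustration on assumed inputs, the low end is negligible, and zero is possible. A reader might go on to doubt the trial's remission result. The protocol gives no ground for that, since remission is defined by drug need and does not use HOMA or the insulin assay. The change is worth making before analysis, because it needs only data already collected.

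**What to change.** In the Statistical analysis section:

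1. Restrict the between-arm repeated-measures analysis of measured insulin and insulin-based HOMA to patients not on insulin at baseline, defined from the insulin variable already recorded. Do not define the subset by insulin use after surgery, because that would select on an outcome.
2. Add a sensitivity analysis for patients in that subset who start insulin after surgery, since the baseline restriction does not cover them.
3. For the whole randomised population, base statements about own secretion on the C-peptide results already planned. If an index is wanted for everyone, build it from fasting glucose and fasting C-peptide.
4. State that HOMA is computed from fasting glucose and fasting insulin, since both fasting and two-hour values are collected.

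The cost is wording plus some precision: no new samples or visits, but fewer patients in the insulin and HOMA comparisons. Under the assumed 10% to 30% insulin users, 14 to 18 of 20 per arm would remain before drop-out.

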***Evaluation of hormonal change**

(1) blood sampling and centrifuge for plasma

Sampling at follow up point

Keep 8hr of NPO, storage in EDTA tube, centrifuge at 4℃, 1600 x g for 15 minutes. Keep plasma at -70℃

(2) Radioimmunoassay (RIA)

<commercial RIA kits>

Ghrelin과 Leptin (Linco Research, St. Charles, Missouri)

GLP-1과 NPY (Interscience Institute, Inglewood, CA)

Glucagon, IGF-1 (Endocrine Sciences Inc., Calabasas, CA)

1. **Estimated side effects of this study**

No specific additional risk

Same as standard gastrectomy

1. **Trial drop-out and stop**

When participant withdraw his/her agreement

1. **Analysis and interpretation**

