**The mechanism of improving diabetes by surgery**

Basically reducing oral intake and nutritional absorption in GI track is a mechanism of improving hyperglycemia by surgery. In addition, various hormones such as GLP-1, IGF-1, Leptin, CCK, Ghrelin, Neuropeptide Y, which is changed its level bypassing food can lead the improvement of impairment of insulin and hyperglycemia.

1. **The upper intestinal hypothesis**

There is a theory for the improvement of hyperglycemia for patients receiving metabolic surgery: if food does not pass through duodenum (food does not contact any upper GI mucosa), an unknown-hormone which related insulin resistance, is not secreted, consequently, it can improve hyperglycemia. A study showed that duodeno-jejunal bypass (DJB) could improve DM without notable weight loss or the amount of diet. Also another study showed that excluding duodenum for food passage led improving DM, but re-including duodenum led recurrence of DM. Another study which can valid this theory showed that endoluminal duodenal sleeve which prevent the contact between duodenal mucosa and food lead improving DM.

[figure not shown]

Proximal bowel hypothesis: When excluding proximal bowel including duodenum for food passage lead improving DM (Rubino et al. Ann Surg, 2008)

1. **The lower intestinal hypothesis**

RYGB and BPD procedure makes early contacting food to distal small bowel and it lead secretion of GLP-1, one of incretin peptide and this mechanism would be related to improving DM. GLP-1 induces glucose-dependent insulin secretion and inhibits glucagon secretion, and delays gastric empting. Also, it induced increasing mass of beta-cell in *in vivo* model. GLP-1 is stimulated by nutritional contacting at L-cell in ileum and colon and induces inhibition of appetite and reducing glucose level.

[figure not shown]

Distal bowel hypothesis: early contacting food to distal part of small bowel lead secretion of GLP-1 in L-cell and it stimulate the effect of glucagon. (Rubino et al. Ann Surg. 2008)

1. **The ghrelin hypothesis**

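### Hormone samples are handled in EDTA with no peptidase inhibitor named and no limit on time to spin, so GLP-1 (if assayed as intact peptide), and perhaps glucagon, can degrade before assay

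*Protocol*

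**What the plan says.** The second purpose of the trial is "Evaluating the mechanism of DM improvement according to reconstruction type". The background rests one of its three hypotheses, the lower intestinal one, on GLP-1: early arrival of food in the distal bowel is said to "lead secretion of GLP-1, one of incretin peptide and this mechanism would be related to improving DM". The Statistical analysis section lists GLP-1 and glucagon among the hormones compared between arms by repeated-measures analysis of variance.

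The section on evaluation of hormonal change gives a single procedure for these samples: "Keep 8hr of NPO, storage in EDTA tube", a 15-minute spin at 4 °C and 1600 x g, then "Keep plasma at -70" °C. Commercial radioimmunoassay kits follow. The supplier for GLP-1 is given as "Interscience Institute, Inglewood, CA", and the entry for glucagon is "Glucagon, IGF-1 (Endocrine Sciences Inc., Calabasas, CA". The section mentions no inhibitor, no chilling before the spin and no time limit before the spin. It does not say whether the GLP-1 kit reads intact or total peptide.

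The Variables list includes "duration of DM, duration of DM treatment, drug for DM", but does not tie drug use to each blood draw. No diabetes drug class is named anywhere.

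**The concern.** The procedure is specific enough to be followed at the bench: it gives temperature, g-force, spin time and storage temperature. A site that follows it as written would use EDTA alone. EDTA is an anticoagulant and does not stop DPP-4, the enzyme that cleaves intact GLP-1, nor other proteases that may act on glucagon. That is general assay knowledge, not something the protocol states.

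If the kit reads intact GLP-1, the measured value then depends on how long the tube waited. With a small sample, this weakens the trial's ability to say anything about one of its mechanism markers. A null GLP-1 result could not be told apart from handling loss, and peptide lost before freezing cannot be recovered later.

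**Working it through.** **The plan's own figures.** Exact enumeration of the 18 x 18 outcomes for the two-sided likelihood ratio test at 57% v 15% gives power 0.8091 and actual alpha 0.0764, as stated. With 10% drop-out, 18 / 0.9 = 20 per arm, 40 in total. None of these depends on sample handling. They matter here only because they fix the size of the hormone comparison: at 18 per arm a single-time comparison of means has 80% power for (1.960 + 0.842) x sqrt(2/18) = 0.93 SD, and at 20 per arm for 0.89 SD. There is little room for added noise.

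**Loss in the tube.** The documents give no rate, so I assume exponential decay of intact GLP-1 with a half-life of 20 to 120 minutes. Fraction left = 0.5^(delay / half-life).

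| Delay | Half-life 20 min | Half-life 120 min |
|---|---|---|
| 10 min | 71% | 94% |
| 30 min | 35% | 84% |
| 60 min | 12.5% | 71% |

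Two samples with the same true level, spun at 10 and 60 minutes, would differ by a factor of 0.5^(-50/120) = 1.3 to 0.5^(-50/20) = 5.7. That is pure handling noise.

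If every sample lost the same fraction L, the arm difference would become (1 - L) x (true difference), while the arm ratio would not change. Uniform loss therefore shrinks the absolute difference and brings values closer to assay error that does not scale with level. Variable delay adds the extra variance.

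**Possible differential effect.** A DPP-4 inhibitor taken by the patient could protect GLP-1 in the tube. Inputs:

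- Drug-free rates of 57% (Roux-en-Y) and 15% (gastroduodenostomy), from the Sample size section, so 43% and 85% remain on a drug.
- u, the share of patients on a DPP-4 inhibitor before surgery: assumed 0 to 50%.
- L, the loss when no inhibitor is present: assumed 10 to 50%, with full protection while on the drug.

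With no true difference, the Roux-en-Y to gastroduodenostomy ratio is

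[(1 - L) + L x 0.43u] / [(1 - L) + L x 0.85u].

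| u | L = 10% | L = 30% | L = 50% |
|---|---|---|---|
| 0% | 0% | 0% | 0% |
| 10% | -0.5% | -1.7% | -3.9% |
| 30% | -1.4% | -4.9% | -10.0% |
| 50% | -2.2% | -7.6% | -14.7% |

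For the last cell: (0.50 + 0.50 x 0.215) / (0.50 + 0.50 x 0.425) = 0.6075 / 0.7125 = 0.853.

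The same number results if the drug is taken to multiply measured intact GLP-1 by m = 1/(1 - L): with m = 2, (1 + 0.215) / (1 + 0.425) = 0.853. In that reading m covers the drug's effect in the body as well as in the tube, and a tube additive removes only the second part. The -15% end comes from stopping u and L at 50%. It is the end of an assumed range, not a bound.

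**The case against.** The protocol is silent on an additive; it does not rule one out. A kit insert or laboratory manual could supply both additive and timing. This stands as a caution, but the section refers to no such document, and it goes into bench detail without mentioning either.

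The kit may read total GLP-1, in which case the tube effect is small. This also stands, and it makes the point conditional. Adding an inhibitor would still cost little and have almost no downside.

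A reader might infer that the tube biases GLP-1 against Roux-en-Y. The documents do not support that. It needs an intact-peptide assay, material DPP-4 inhibitor use and more stopping of that class after Roux-en-Y, and none of the three is shown. Newly diagnosed patients are eligible and may take no drug. The background gives the 57% as a 1-year figure, so it says nothing about day 7 or 3 months, and no imbalance is expected before surgery.

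A reader might also take GLP-1 as the decisive mechanism marker. It is one of several hormones and belongs to one of three hypotheses. The remission comparison that sizes the trial is unaffected.

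Finally, fasting sampling may matter more. The protocol itself says "GLP-1 is stimulated by nutritional contacting at L-cell in ileum and colon", yet hormone samples are taken after an 8-hour fast, and GLP-1 has no post-prandial value in the Variables list. That is a separate weakness. Inhibitor tubes do not solve it, and it does not excuse uncontrolled handling of the fasting samples.

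**Conclusion.** The point holds in a conditional form. As written, the handling rule leaves GLP-1, if measured as intact peptide, and possibly glucagon, open to loss that varies with an uncontrolled delay. The firmer consequence is a smaller absolute difference and added noise with about 18 to 20 patients per arm: under the assumed half-lives, a 1.3-fold to 5.7-fold spread between spins at 10 and 60 minutes. No size can be given for glucagon.

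A differential effect against Roux-en-Y is a possibility only. Over the assumed ranges it runs from 0% to about -15% of the GLP-1 ratio, and part of it would be a drug effect in the body. A reader might quote a bias of several per cent as caused by the tube; that would need a minimum level of DPP-4 inhibitor use that the documents do not give. The weight is that of a cheap improvement to a secondary purpose, best made before the first draw.

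**What to change.** In the section on evaluation of hormonal change, have GLP-1 and glucagon drawn into chilled EDTA tubes containing a DPP-4 inhibitor and a protease inhibitor compatible with the kit, kept on ice, with a fixed maximum time to centrifugation. In the Variables list, record the diabetes drug class in use at each draw, so that the GLP-1 result can be interpreted.

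Do not use exclusion of samples taken on DPP-4 inhibitors as evidence for an arm effect. It selects on a post-randomisation outcome that the surgery affects: if half of drug users take one, it keeps 1 - 0.43 x 0.5 = 78.5% of Roux-en-Y samples but 1 - 0.85 x 0.5 = 57.5% of control samples. At most, report it as descriptive.

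Cost: inhibitor tubes for at most 40 patients x 4 visits = 160 draws, a short change to the sampling procedure, and one recorded item per draw. Sample size, power and surgery do not change.
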